##### Categories of Auditory Performance (CAP)

CAP is usually used in assessing the auditory condition in patients with hearing loss and the process of recovery after hearing intervention [49]. The original CAP cannot describe the sophisticated listening skills of adults, so we are going to use an extended version of it [50], which consists of ten categories, graded from 0 “No awareness of environmental sounds” to 9 “Use of phone with unknown speaker in unpredictable context,” which will correspond to different auditory receptive abilities.

##### International outcome inventory for hearing aids (IOI-HA)

IOI-HA is an international standard self-report questionnaire developed to quantify the satisfaction of hearing aid users and the improvement of their lives by the application of hearing aids [51]. It consists of 7 questions, including the time of wearing hearing aids, the benefit and satisfaction of hearing aid applications, etc. Each question is ranging from the worst performance 1 to the best performance 5 [52].

##### Cognitive evaluations

Cognitive function encompasses various domains, including basic sensory and perceptual processes, as well as advanced executive function and cognitive control abilities [53]. To conduct a comprehensive evaluation of patients’ cognitive function, we plan to utilize a series of assessment scales. These questionnaires have previously been translated into Chinese and are commonly used in clinical settings. All evaluations of the patients’ cognitive will be performed at our study centers by our researchers and will not be disturbed by other things.

##### Mini-mental State Examination (MMSE)

MMSE consists of temporal and spatial localization, word retelling, calculation, language use, comprehension, and basic motor skills [54], which has been the most common method for decades to detect the presence of cognitive decline [55]. It will be performed in the screening phase of the study. And although hearing loss will not conduct a significantly additional impact on the scores of MMSE result [56], we will raise the volume of the conversation with participants properly, ensuring that participants will hear the evaluation contents correctly.

##### Clinical Dementia Rating (CDR)

CDR is widely used in the measurement of the patient’s cognitive impairment, which consists of evaluations in six domains (memory, orientation, judgment and problem-solving, community business, home and hobbies, personal care). The score of 0 in CDR represents normal, while 0.5 represents MCI or suspected dementia and 1, 2, and 3 represent mild, moderate, and severe dementia [57].

##### Alzheimer’s Disease Assessment Scale-Cognitive section (ADAS-Cog)

ADAS-Cog is usually performed to evaluate the cognitive and behavioral functions in patients impaired by Alzheimer’s disease (AD) and is considered to be the gold standard for evaluating the efficacy of dementia treatment [58]. The scale is made up of 11 subscales designed to assess a variety of cognitive abilities, including memory, speech, and practice, which are often thought to be the features in the development of AD [59]. In our study, we will select the Chinese translation version with 12 items and add the item of attention, which also passed the reliability and validity analysis [60].

The minimal clinically relevant change (MCRC) on the ADAS-Cog for patients with AD is usually among 3 to 5 points. 4 points are recommended by the FDA as the appropriate MCRC for clinical trials of patients [61].

##### Other evaluations

**Geriatric Depression Scale (GDS)**

Depression is usually suggested being a risk factor and a prodromal symptom of dementia [62]. So we will use the original GDS, a 30-item self-report scale, to assess the situation of depression in our subjects, which helps us distinguish it in MCI patients with more than 10 points [63, 64]. The scale represents features of depression in older adults in both emotional (e.g., sadness, crying, loneliness) and cognitive areas (e.g., hopelessness, helplessness, guilt) [65].

**Activity of Daily Living Scale (ADL)**

ADL-14 consists of 14 questions, involving the whole set of behaviors of people in daily life, devised for evaluating the activity functional state of individuals systematically and personalized by asking their family numbers. The higher score on ADL-14 indicates greater functional disability [66].

**Functional activities questionnaire (FAQ)**

FAQ is commonly used to assess the functional limitations in older adults [67]. The questionnaire contains 10 questions for evaluating complex cognitive functions and social activities. It consists of handling finances, purchasing daily necessities, preparing meals, the attention to events broadcast in the media, etc., ranging from 0 (independent) to 3 (dependent on others totally) in each content. A score of 9, meaning the subject is completely dependent on others in at least 3 domains, is suggested functional impairment in patients [68]. We will interview their family members to obtain the information.

**Short Form-12 (SF-12)**

The SF-12 is the shortened alternative to the SF-36, containing 12 subsets. It is often used to evaluate the living quality of participants with a focus of whole physical and mental health outcomes [69, 70].

##### Vital signs and blood glucose

According to the previous study, cumulative blood pressure is one of the risk factors in dementia with negative cognitive effects [71]. And high blood glucose is associated with the risk of unspecified dementia [72]. Therefore, we will measure the subjects’ pulse, blood pressure, and glucose to determine whether subjects have any underlying disease. Furthermore, these data will also suggest the physical states of patients to monitor whether serious adverse events occur.

### Adverse events

No foreseeable adverse events related to hearing aid fitting are expected to occur in the study. However, in the event of any unexpected adverse events, they will be documented and reported following the standard operating procedures set forth by the Ethics Committee of Shanghai Ninth People’s Hospital.

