### Intervention

After randomization, every participant allocated to the hearing aid fitting group will get the binaural and behind-the-ear hearing aids, Widex-Evoke E-FA100 & E-FP50, with a full set of auxiliary accessories, purchased by Ninth People’s Hospital and distributed to each sub-center. Our professional audiologist will make adjustments for patients until they can hear what others say with a few noisy environmental sounds, which will make participants willing to learn the usage of hearing aids and wear them in their daily lives. In addition, some of the subjects with a long history of hearing loss may lead to poor effect of hearing aids. We will provide some suggestions on hearing rehabilitation for them, including reading newspapers out and talking to their families frequently. Patients are required to wear hearing aids for more than 10 h per day. The time of wearing hearing aids will be recorded by a system; thus, we can remind subjects. Furthermore, participants will maintain their hearing aids if needed and make regular adjustments to their hearing aids with the help of an audiologist.

The patients in the health education group will receive periodic health education from researchers as part of the study, including valuable guidance on hearing health, such as the importance of noise reduction, avoidance of ototoxic drugs, and development of healthy ear care habits.

Furthermore, we will make it clear to the participants that those who are allocated to the intervention group will benefit from using hearing aids free of charge for the rest of their lives, while those who are assigned to the control group will receive an extra allowance at the end of the trial period. Besides, in the hearing aids group, we will use the system in hearing aids to record the average duration of hearing aid use, and for those who do not meet the requirement, we will take measures such as the commissioning of hearing aids and online supervision. All participants will get subsidies for the cost of transportation for every follow-up visit.

In the follow-up stage, the patients of the two groups will be recalled to study centers to perform assessments of auditory tests and cognitive evaluations at 6, 12, and 24 months after the intervention. Researchers will contact those who are near the date of the follow-up visit and make an appointment with them in advance.

Subjects are not allowed to participate in another trial which may influence the results during the study.

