#### Primary outcome measure

The primary outcome of the study is the rate of patients with ARHL and MCI progressing to dementia in two groups after different interventions.

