### Blinding

Blinding is not possible in this study due to the nature of the intervention for participants or researchers, but we intend to blind the data analyzers to reduce bias in the data analysis. Moreover, we will employ several strategies to mitigate bias from both researchers and participants. Firstly, prior to their involvement in the CHOICE project, researchers will receive standardized training to ensure consistent data collection and analysis. Additionally, we will utilize standardized measurement tools and quality control procedures to monitor data accuracy and reliability. Furthermore, we will ensure that participants in both the intervention and control groups are well-informed about the potential benefits and drawbacks of their respective treatments, aiming to minimize biases in their perceptions of therapeutic effects.

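### The only commitment to document adverse events covers 'unexpected' ones, a term left undefined, so harms may be under-recorded and picked up unequally between the arms

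*Protocol article*

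**What the plan says.** The Adverse events section has two sentences. The first states: "No foreseeable adverse events related to hearing aid fitting are expected to occur in the study". The second sets the recording duty: "in the event of any unexpected adverse events, they will be documented and reported" under the Ethics Committee's standard procedures. The section gives no definition of 'unexpected' and no list of anticipated events.

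Four other sections bear on this:

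- **Intervention**, on wear: "Patients are required to wear hearing aids for more than 10 h per day". Wear time is logged by the device, and "for those who do not meet the requirement, we will take measures such as the commissioning of hearing aids and online supervision".
- **Intervention**, on contact: aid users have initial fitting and regular adjustment with an audiologist. Controls receive periodic health education. Both arms are recalled at 6, 12 and 24 months.
- **Blinding**: neither participants nor researchers are blinded; only the data analysts are meant to be. Participants in both arms are to be "well-informed about the potential benefits and drawbacks of their respective treatments".
- **Vital signs and blood glucose**: pulse, blood pressure and glucose are measured to look for underlying disease, and "these data will also suggest the physical states of patients to monitor whether serious adverse events occur".

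**The concern.** Expectedness normally decides how an event is reported onward, not whether it is written down. Here the one sentence that creates a duty to document makes expectedness the entry condition and leaves the term to each member of staff. The sample size section assigns quotas to three hospitals (516, 103 and 69 participants), so the same complaint could be recorded at one and not at another.

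At stake is the harm side of the trial. The external committee is to review provisional data after the first year, and stopping may be considered if the interim result is positive. What can be said about harms then, or at 24 months, depends on what sites were told to record.

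**Working it through.** The Adverse events section contains no figure, so there is no calculation to reproduce. The check sets the passages side by side.

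**Step 1. What the recording sentence covers.** It can be read in two ways.

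| Kind of event | Broad reading: nothing is expected, so everything is unexpected | Narrow reading: unexpected means surprising to staff |
|---|---|---|
| Ordinary complaint from wearing the aid | Recorded | Need not be recorded |
| Death, admission or fall in a person aged 60 or over with MCI | Not settled (see below) | Need not be recorded |
| Surprising event of any kind | Recorded | Recorded |

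The broad reading rests on the first sentence, which empties the set of expected events. That sentence speaks only of events related to hearing aid fitting. It does not say that nothing else is foreseeable over 24 months in this population. Even on the broad reading, then, the duty is not clearly extended to foreseeable events unrelated to the device.

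**Step 2. Where a tolerability problem would go.** Suppose a participant finds the aid uncomfortable and wears it for less than the required time. The Intervention section responds with reminders, readjustment and online supervision. Nothing there or in the Adverse events section asks for the reason, or links the response to an adverse-event record. The problem can pass through the trial purely as an adherence matter.

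**Step 3. Opportunities to report, by arm.** The three follow-up visits are common to both arms. Beyond them, aid users have audiologist adjustments, reminders and online supervision; controls have periodic education. Staff know the allocation. Let p1 and p0 be the true event proportions in the aid and control arms, and c1 and c0 the chances that an event is recorded. Then

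recorded ratio = (p1 × c1) / (p0 × c0) = true ratio × (c1 / c0).

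Extra contact tends to raise c1. Handling complaints as adherence tends to lower it. Nothing in the document makes c1 equal to c0, so neither the size nor the direction of the distortion is known.

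**Step 4. Whether vital signs fill the gap.** The text offers them as an additional indication of serious events, not as the only means of finding them. They would not show a local ear complaint. If they are taken at the scheduled visits, they would not by themselves identify a fall or admission between visits.

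**Step 5. Size.** The rule applies to all 688 planned participants (344 + 344; by site 516 + 103 + 69 = 688). The documents give no event rate and no capture rate, so the number or share of missed events cannot be derived.

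**The case against.** The strongest reply is that the text does not exclude anything. If the protocol expects no events, any that occurs is unexpected and is documented. Procedures are referred to the Ethics Committee, and a full protocol exists that is not shown, so question sets, definitions and collection windows may properly sit there. No safety outcome or between-arm safety comparison is stated, so no safety claim is at risk. Wear problems are not invisible either, since wear time is logged and the IOI-HA asks about benefit and satisfaction.

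Much of this stands. A reader might infer that wear-related problems will certainly go uncounted, or that the safety result is bound to look clean. The document does not support either: both depend on the narrow reading, and no safety result is defined. The promise to explain drawbacks might be read as contradicting the claim that nothing is foreseeable. It is only awkward, because it covers both arms and a drawback need not be an adverse event. Nor do the remarks on noise exposure as a risk factor, or on tympanometry as an eligibility test, say that hearing aids cause harm.

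What the reply does not dispose of is the wording. The referral to Ethics Committee procedures is attached to unexpected events only, so it does not widen the duty. The broad reading reaches only events related to fitting. The point therefore concerns a rule the article states, not detail that it leaves out.

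**Conclusion.** The point holds as a flaw of wording with a cheap remedy. The sole documentation duty is tied to an undefined term. On a fair narrow reading it omits ordinary wear complaints and foreseeable events in older adults, and on the broad reading the latter remain unsettled. With low wear treated as adherence and with unequal, unblinded contact, events may be under-recorded and ascertained differently by arm.

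The size is unknown, and any figure for missed events would be invention. The conclusion assumes that sites follow the published sentence; a full protocol that already requires all events to be recorded in both arms would reduce this to correcting the article. No effect on the primary comparison of progression to dementia is shown.

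**What to change.** In the Adverse events section:

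- Delete 'unexpected' and the statement that no events are foreseeable.
- Record all adverse and serious adverse events, including deaths, hospital admissions and falls, in both arms from randomisation to 24 months, whatever their expectedness.
- Ask the same short set of questions in both arms at the existing 6-, 12- and 24-month visits.
- Flag events noted only at extra audiologist contacts, so that a comparison restricted to common visits is possible.
- Record the stated reason whenever wear time is below the requirement.
- Tabulate events by arm.

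Reporting change in pure-tone threshold by arm, from the audiometry already repeated at follow-up, is an optional addition.

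The cost is an amendment, a short form and a few minutes per visit, with no new visit or test. The safety table may look less favourable. Enrolment began in September 2021, so the date of the change should be stated beside the table.

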### Participants’ withdrawal

Participants have the right to withdraw from the study at any time without providing a reason. Any participants who are lost to follow-up will be recorded, and an intention-to-treat analysis will be performed exclusively for these individuals.

### Blinding

Blinding is not possible in this study due to the nature of the intervention for participants or researchers, but we intend to blind the data analyzers to reduce bias in the data analysis. Moreover, we will employ several strategies to mitigate bias from both researchers and participants. Firstly, prior to their involvement in the CHOICE project, researchers will receive standardized training to ensure consistent data collection and analysis. Additionally, we will utilize standardized measurement tools and quality control procedures to monitor data accuracy and reliability. Furthermore, we will ensure that participants in both the intervention and control groups are well-informed about the potential benefits and drawbacks of their respective treatments, aiming to minimize biases in their perceptions of therapeutic effects.

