
### Outcome measurements and follow-ups

The assessment of the following outcomes will take place during the screening, baseline measurements, and follow-up visits at 6, 12, and 24 months after the intervention (refer to Table 1). Our researchers will conduct all measurements using the same standardized procedures.

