### Quality control

Researchers, including audiologists, cognitive evaluators, and data collectors, will be required to ensure full compliance with specifications and pass the consistency test during the assessment process. Additionally, 5% of the subjects will be randomly selected for audio recording of the entire cognitive evaluation process, which will be submitted to the Shanghai Mental Health Center for quality control.

An external data monitoring committee will monitor the study. The committee will be independent of the sponsor and researcher in the study and have no competing interests. The committee will have an audiologist, a psychiatrist, and a statistician, who will review the provisional data when the completion of data collection for the first year. The implementation of projects will be tracked and reviewed by the Ethics Committee of Ninth of Shanghai Ninth People’s Hospital every year.

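### The protocol rules out blinding for all researchers, but the cognitive evaluators need not know allocation; the listening condition at follow-up testing is also not stated

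*Protocol article*

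**What the plan says.** All references are to the protocol article.

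- **Blinding:** "Blinding is not possible in this study due to the nature of the intervention for participants or researchers". The sentence continues "but we intend to blind the data analyzers to reduce bias in the data analysis". The further measures named there are training, standardized tools, quality control, and balanced information to participants.
- **Outcome measurements and follow-ups:** "Our researchers will conduct all measurements using the same standardized procedures".
- **Cognitive evaluations:** the assessments "will be performed at our study centers by our researchers and will not be disturbed by other things".
- **Quality control:** the staff are listed as "Researchers, including audiologists, cognitive evaluators, and data collectors" and must pass a consistency test. In addition, "5% of the subjects will be randomly selected for audio recording of the entire cognitive evaluation process", for review by the Mental Health Center.
- **Randomization:** senior researchers enrol participants and assign them according to the card drawn.
- **Mini-mental State Examination (MMSE):** "It will be performed in the screening phase of the study", and for this test "we will raise the volume of the conversation with participants properly, ensuring that participants will hear the evaluation contents correctly".
- **Clinical Dementia Rating and ADAS-Cog:** neither section mentions audibility.
- **Primary outcome measure:** the rate of progression to dementia in the two groups. The section names no instrument or adjudication step.

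**The concern.** The reason given for leaving researchers unblinded fits only some of them. A participant knows whether a hearing aid was issued, and the audiologist who fits it knows too. A person who comes in only to administer and score cognitive tests need not know. By treating all researchers as one class, the protocol gives up masking where it was available, on the outcomes that depend most on a rater's judgement.

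Rater expectation would be likely to favour the hearing-aid arm. The endpoint is a dementia classification, and the planned difference is 8 percentage points (10% against 18%), so a few points of differential rating would matter. The Statistical methods section adds to the stakes: a positive 12-month interim result may lead to termination of the study.

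Audibility raises a related question. Participants have a pure tone average of 35 to below 80 dB HL. If the two arms heard the follow-up tests under different conditions, the intervention could change the measurement as well as the cognition. The article does not say what those conditions are.

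**Working it through.** **1. Who knows the allocation, and who rates.**

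| Role | Section | Must know allocation because of the intervention? |
|---|---|---|
| Participant | Blinding | Yes |
| Senior researcher who enrols and reads the card | Randomization | Yes |
| Audiologist who fits and adjusts the aids | Intervention | Yes |
| Cognitive evaluator | Quality control; Cognitive evaluations | No reason given |
| Data analyst | Blinding | No; masked |

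The first four are covered by the statement that blinding is not possible. The stated reason applies to the first three.

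**2. Whether the stated safeguards mask allocation.** Training, standardized tools and the consistency test make raters more alike, but they do not remove knowledge of the arm. The audio recording covers 5% of subjects (0.05 × 688 ≈ 34) and is not described as a masked re-rating.

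**3. Audibility.** The one stated step is under the MMSE, which is placed in the screening phase, before randomization. The general Cognitive evaluations section promises only freedom from disturbance. The visit schedule (Table 1) is not available in the text reviewed. The finding is therefore that the follow-up listening condition is not stated.

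**4. The plan's own figure.** With p₁ = 0.10, p₂ = 0.18, two-sided α = 0.05 (sidedness is not stated; two-sided fits) and power 0.80, the unpooled formula is

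n = (1.960 + 0.842)² × [0.10 × 0.90 + 0.18 × 0.82] / 0.08² = 291.4, rounded up to 292 per arm.

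This matches. The pooled formula gives 295. With drop-out, 292 / 0.85 = 343.5, rounded up to 344, and 2 × 344 = 688.

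**5. Illustration of what differential rating could do.** The inputs e and the one-sided pattern are assumptions that are not in the document.

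Suppose there is no true effect and the true risk is 18% in both arms. A share e of non-demented controls is wrongly rated demented, and no aided participant is. The observed control risk is then 0.18 + 0.82e. For n = 292 per arm:

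- d = 0.82e
- SE₀ = √[2p̄(1 − p̄)/n], where p̄ is the mean of the two observed risks
- SE₁ = √[(p_c(1 − p_c) + 0.18 × 0.82)/n], where p_c is the observed control risk
- P(reject) = Φ[(d − 1.96·SE₀)/SE₁] + Φ[(−d − 1.96·SE₀)/SE₁]

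| e | Observed control risk | d (points) | SE₀ | SE₁ | P(reject, two-sided) |
|---|---|---|---|---|---|
| 0 | 18.0% | 0 | 0.0318 | 0.0318 | 0.050 |
| 0.03 | 20.46% | 2.46 | 0.0326 | 0.0326 | 0.117 |
| 0.05 | 22.1% | 4.10 | 0.0331 | 0.0331 | 0.235 |

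A second pattern, in which bias lowers the observed rate in the hearing-aid arm from 18%, gives these chances of a significant result favouring hearing aids: 2.5% with no bias, 5.0% at 1 point, 9.4% at 2 points, 16.3% at 3 points and 38.5% at 5 points.

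If the same share e were misclassified in both arms, both observed risks would be 0.18 + 0.82e, d would be 0, and there would be no false benefit. The result depends entirely on the misclassification being differential.

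**The case against.** The strongest case on the other side concerns audibility. A reader might infer that the follow-up tests are taken aided in one arm and unaided in the other, and that the hearing-aid arm will therefore score better because it hears the questions. The article does not say this. The requirement to wear aids more than 10 hours a day makes aided attendance plausible, but nothing is said about aids at testing or about amplification for controls. All measurements are to follow the same standardized procedures, and the MMSE section shows that the team has thought about audibility. Placing the MMSE at screening does not prove that it is never repeated. Details of test administration are also what an article may leave to the full protocol. This objection stands, so audibility is an open question here and not a demonstrated bias.

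A reader might also infer that both biases reach the primary outcome and all cognitive scales. The protocol names no instrument for dementia, so the path from a misheard question to the endpoint is an inference. The ADL and FAQ draw on family members, so participant audibility matters little there, though rater expectation could still act.

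The 3–5% misclassification has no source in the document, and placing all of it in controls is an unfavourable choice. That also stands.

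The objection does not answer the rater point. The training, the consistency test and the 5% recording are genuine quality measures, but none hides allocation. The lack of rater masking is stated in the protocol; it is not a detail left for another document.

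**Conclusion.** The concern holds for the raters. The protocol declares masking impossible for a group that includes cognitive evaluators, and the reason it gives does not apply to them. Unmasked rating of dementia and cognition can therefore favour the hearing-aid arm.

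For audibility the conclusion is weaker: the listening condition at the 6, 12 and 24 month tests is not stated, so differential audibility is a possible further bias.

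The document gives no basis for the size of either. The false-positive rate of 12–24% instead of 5% is an illustration that rests on four assumptions: no true effect, 18% true risk in both arms, 292 analysed per arm, and 3–5% misclassification confined to controls. It shows that a distortion of 2.5 to 4.1 points, well under the planned 8-point difference, would matter. It does not show that one of that size will occur, or that a positive result would be uninterpretable.

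**What to change.** 1. In the Blinding section, replace the statement that researchers cannot be blinded with a rule for the cognitive evaluators: they take no part in recruitment, card allocation or fitting; they are not told allocation; and participants are asked before each assessment not to reveal it. Participants and fitting audiologists remain unblinded.
2. In the Cognitive evaluations section, state one audibility check for the remaining follow-up visits, such as a short word-repetition check, applied in the same way in both arms before testing begins.
3. Report visits completed before the change as unmasked.

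**Cost.** The first item reassigns existing roles, and the second adds a short step to each visit. Masking will be imperfect, because participants may disclose their arm or be seen with aids. The first participant was enrolled on 28 September 2021 and Version 3 is dated 18 November 2023, so the earliest 24-month visits were already falling due and many baselines were already done. A new testing procedure at baseline cannot be applied to those participants, so the change is limited to visits still to come.
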